### Recruitment {15}

#### Screening

All patients receiving maintenance haemodialysis in renal units across the Northern Territory undergo a series of clinical laboratory tests (haematology and serum chemistry) at the commencement of the month as part of routine care. These results are used to screen potential participants for eligibility into the study.

The treating renal team is approached for a discussion on potential recruitment of the patients into the trial, and for permission to review the patient’s medical notes. The study team assesses the eligibility criteria and completes the Pre-Screening Case Report Form (CRF). If ineligible, the patient is not approached. If considered eligible, the patient is approached for an informed consent discussion using the teach back method to determine if an interpreter is required to obtain consent. After consent is obtained, eligibility will be re-established prior to randomisation. Each unit maintains a log of all pre-screened patients along with their eligibility and consent outcomes in the medical records or notes. However, should a potential participant consent meet the temporary exclusion criteria at time of screening they will be re-approached for inclusion into the trial at a subsequent clinic visit.

To maximise recruitment, the research team spends a considerable time in the renal units providing information and education to potential participants using the teach back method. There is also a potential for expanding the recruitment to other renal units across Northern Australia to achieve the desired sample size.

## Assignments of interventions: allocations

### Sequence generation {16a}

Prior to proceeding with randomisation, the research nurse and/or investigator ensures informed consent has been obtained and documented and confirm that the participant is eligible to be enrolled. Participants are randomised using a module in the web-based study database, the Research Electronic Data Capture (REDCap) that is password protected and stored on a secure drive at Menzies School of Health Research. Compulsory fields required prior to randomisation are screening number (Study Identification number), confirmation of eligibility, age, hospital registration number (HRN), confirmation of consent, recruitment site (unit) and ferritin strata. Randomisation will be stratified by location (Top End and Central Australia) and ferritin strata (≤ 1200 μg/L and > 1200 μg/L) and will be in permuted blocks of variable block size. Participants are randomised in a 1:1 ratio to either Arm A: Intervention treatment group or Arm B: control group via REDCap, available 24 h per day, 7 days per week (Menzies School of Heath Research, Darwin).

### Concealment mechanism {16b}

The randomised sequence allocation is stored on the password-protected secure server by the trial statistician and will not be available to any investigators or member of study staff.

### Implementation {16c}

Randomisation is performed at the site with allocation occurring via the web-based database (REDCap), this only occurs after informed consent is obtained and eligibility confirmed. Participants are enrolled by Investigators or research nurses that have been delegated this responsibility by the principal or chief investigator (CI). To randomise the participant, the research nurse or investigator logs onto REDCap and enters the details required to obtain the treatment randomisation number assigned to the participant for that site.

## Assignment of interventions: blinding

### Who is blinded {17a}

This is an open-label blinded end point assessment trial. The intravenous iron treatments are supplied by a central pharmacy, either at the Royal Darwin Hospital or the Alice Springs Hospital and is prepared and administered by the nursing staff as per routine clinical care. The patient, nurses administering the drugs and investigators will not be blinded to the treatment allocation. The administration will be direct into the dialysis circuit as per the standard intravenous iron administration procedure on haemodialysis.

The investigators assessing and analysing the primary outcomes (see below—outcomes assessment committee) are blinded to treatment allocation. Independent outcomes Assessors not involved in any aspect of the study will review and complete a data collection form of all randomised study participants to independently determine the study outcomes (from both electronic and written medical records). In view of the relationships likely to develop between the research staff and some of the participants, it is essential that we engage independent outcomes assessors. The outcome assessment data collection forms and final assessment will be verified by two of the chief investigators.

### Procedures for unblinding outcomes if needed {17b}

This is an open-label blinded end point assessment trial. However, an Independent Data Safety and Monitoring Board (DSMB) reviews safety data, including serious adverse events and the primary endpoint events, and will advise on continuation of the study, or whether the study should be stopped prematurely because of safety concerns. In a closed session, the DSMB will be provided with descriptive analyses of study data by study labels “A” and “B” for the allocated treatment arms.

## Data collection and management

### Plans for assessment and collection of outcomes {18a}

#### Demographic and clinical data

A full and relevant clinical and social history will be obtained from each participant. Key factors of direct interest for this study include time on dialysis, dialysis access and dialysis access interventions, ideal dry weight, height, body mass index, waist hip ratio, primary renal diagnosis, comorbidities (liver, lung, diabetes, cardiovascular, etc.), current smoking status, history of current or previous alcohol intake, dietary history, any significant illnesses, previous Hb levels, a full medication list and history, and sociodemographic data.

#### Major events

Hospitalisation due to all-cause infections or death are documented as the primary outcome. All admissions overnight or longer are followed up with collection of detailed data on the admission. Data on all major vascular events, all dialysis access-related events including infections and vascular interventions not requiring hospital admission are also collected.

#### Data collection from routine care: routine blood tests

Haemodialysis patients have monthly blood tests as part of their routine care. Tests obtained as part of this routine screen that are analysed as outcomes and covariates of interest for this study include: Hb, CRP, full blood count (will include MCV and MCHC), liver function tests, iron studies (ferritin and TSAT), measures of dialysis adequacy (Urea reduction ratio and KT/V (a number calculated from change in urea pre- and post-dialysis, time on dialysis and volume of distribution of urea used to quantify dialysis adequacy). Every 3 months the following are also routinely collected: parathyroid hormone levels and glycated haemoglobin (HbA1c).

#### Additional blood tests

*Samples are collected at baseline and at 12 months for* (1) other measures of iron status (serum hepcidin levels, soluble transferrin factor levels, percentage hypochromic red cells, reticulocyte haemoglobin content) [2]; other causes of anaemia (thyroid function tests, vitamin B12 and folate (only at baseline) [3]; inflammatory markers (serum tumour necrosis factor (TNF) alpha, interleukin-1 (IL-1) and interleukin-6 (IL-6); and [4] and marker of the metabolic syndrome (serum total adiponectin).

#### Assessment of the comparability of the two ferritin concentration measurement methods

*From samples collected at around 1 month comparison of the* Abbott ARCHITECT i1000 (Abbot Diagnostics, USA) versus the Vitros Ortho® XT7600 in a sample of about 150 participants covering the analytical range and above of serum ferritin levels. Ferritin concentrations in the NT have previously been determined using the Abbott ARCHITECT which is the platform used by most laboratories in Australia. Territory Laboratories have recently changed to and now routinely use the Vitros Ortho Clinical Diagnostics platform for analyses of all biochemical analytes. The Vitros Ortho XT7600 gives ferritin concentrations results up to 40% lower than the Abbott ARCHITECT platform.

#### Determination of iron overload

In addition to serum ferritin and TSAT levels, liver iron levels will be determined by use of the non-invasive but accurate method, the magnetic resonance imaging (MRI)-based technique spin-density projection-assisted (SDPA) R2- MRI (FerriScan®) at baseline and at 12 months.

#### Other data from routine care

All patients are routinely followed up by their nephrologist every 3 months, and data from these follow-up appointments is reviewed.

#### Additional follow-up for the study

All participants have medical reviews by the study team at 3, 6, 9, 12, 15, 18, 21, 24, 27, 30, 33 and 36 months (primary outcome assessment).

#### Blinded endpoint assessment and adjudication

The composite primary endpoint is assessed by an independent blinded endpoint adjudication committee. This committee consists of three nephrologists appointed by the trial management committee. This committee is provided with an extract of study data that does not contain patient identifiers and does not contain any mention of treatment allocation or any detail about treatment of any kind, but does contain data relating to adverse events, procedures and concomitant medication changes linked to the primary and secondary outcomes of the study:
Demographic details (such as age and gender)ComorbiditiesClinical detailsDate and result of all blood resultsDate and result of all other available clinical informationHospitalisations and/or deaths

The members of the committee may request more information if needed, but this will only be provided if it is available and does not provide direct or indirect evidence of treatment allocation. Each of the three members of the committee will then independently determine if, in their view, the patient has met the primary endpoint. If there is a discrepancy between the three assessments, the majority will determine the endpoint.

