### Interim analyses {21b}

The DSMB will conduct an interim analysis after 288 patients have been randomised (i.e. at 50% recruitment) and followed for 24 months (2 years) following the date of the first patient randomised.

The interim analysis will review outcome data and answer the following questions:
Are there any significant safety issues that may present an ethical issue in continuing the study? This may include adverse events, but also study conduct and protocol violations.Is there overwhelming data suggesting the superiority of one arm that may present an ethical issue in continuing the study?Using the Haybittle-Peto rule, and the differences according to treatment allocation in risk of hospitalisation with all-cause infection or death as the outcome of interest, the study will be stopped early if there are differences according to treatment allocation in risk of hospitalisation with all-cause infection or death rate with a *p* value of less than or equal to 0.001.3.Are there any other factors that may impact on the feasibility / usefulness of the study? For example, rate of enrolment, unexpected low rate of outcomes, unable to fund and protocol violations.

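### Blinded assessment of the primary endpoint is not secured by the procedures as written: the adjudication extract includes serial iron indices, and the assessors' sources and the chief investigators' verification are not masked

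*Protocol article*

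**What the plan says.** Under Blinded endpoint assessment and adjudication, the protocol article states: "The composite primary endpoint is assessed by an independent blinded endpoint adjudication committee". The committee has three nephrologists who judge independently. On disagreement the rule is: "If there is a discrepancy between the three assessments, the majority will determine the endpoint".

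The committee works from an extract that "does not contain any mention of treatment allocation or any detail about treatment of any kind". The same sentence adds that it "does contain data relating to adverse events, procedures and concomitant medication changes linked to the primary and secondary outcomes of the study", and the list that follows includes all blood results with their dates. Members may ask for more, but only material that gives no direct or indirect clue to allocation is released.

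Under Who is blinded {17a}: "The patient, nurses administering the drugs and investigators will not be blinded to the treatment allocation". That section then says that the investigators who assess and analyse the primary outcome are blinded, and points to the outcomes assessment committee. Separate independent assessors determine outcomes "from both electronic and written medical records". The data collection forms and "final assessment will be verified by two of the chief investigators".

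**The concern.** The trial is open label, so treating staff know the arm when they admit and code a patient. Masked assessment is the main safeguard for the part of the primary endpoint that needs judgement, namely whether an admission was for infection. Death needs little judgement, so the exposure lies in the infection-hospitalisation component.

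The test for indirect evidence is applied to later requests but not to the initial extract, which contains the markers most likely to fail it. The assessors' sources and the chief investigators' verification are two further routes by which knowledge of the arm could reach the endpoint decision. If calls leaned by arm, the primary hazard ratio would shift, in either direction, without any true effect.

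**Working it through.** **Passages side by side**

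1. Routine blood tests are monthly and include haemoglobin, ferritin and TSAT (Data collection from routine care: routine blood tests). An extract holding all blood results holds these series for up to 36 months.
2. Ferritin and TSAT decide each month whether study iron is given, withheld or replaced by rescue iron (Intervention description {11a}; Rescue therapy; Withholding of therapy).
3. Haemoglobin change is the first secondary outcome, and ferritin and TSAT are tertiary outcomes compared between arms. The plan itself thus treats them as markers that may differ by arm.
4. Data management {19} names hospital records, including current medications, as source documents, and the medication chart as the source for compliance. Assessors who read those records can meet iron administration directly.
5. Chief investigators sit on the teams that run the trial day to day (Composition of the coordinating centre and trial steering committee {5d}). No sentence says that the two verifiers are masked or what verification may change.

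**The plan's own figure (not disputed)**

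Inputs from Sample size {14}: 60% versus 48% at 2 years, 5% drop-out, 576 in total. Two-sided 5% is assumed.

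- HR = ln(1 − 0.48)/ln(1 − 0.60) = 0.714.
- Events = 576 × 0.95 × (0.60 + 0.48)/2 = 295.
- Power (Schoenfeld) = Φ(√295/2 × |ln 0.714| − 1.96) = 0.826, so the stated power above 80% is reproduced.

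**How well could the arm be guessed?**

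For one normally distributed marker separated by d standard deviations, with equal arms, the share guessed correctly is Φ(d/2).

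- Haemoglobin, from Sample size {14}: d = 5/11.3 = 0.44, so Φ(0.22) = 59%.
- Ferritin and TSAT: the document gives no separation. Assumed d = 1 gives 69%, and d = 2 gives 84%.

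**What could that do to the result?**

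Assume no true effect, 60% events in both arms, and 1 in 20 events called non-infection in patients guessed to be in Arm A. With a the share guessed correctly:

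- Arm A: pA = 0.60 × (1 − 0.05a)
- Arm B: pB = 0.60 × (1 − 0.05(1 − a))
- Apparent HR = ln(1 − pA)/ln(1 − pB)
- Chance of a significant result = Φ(t − 1.96) + Φ(−t − 1.96), where t = √(D/4) × |ln HR| and D = 547 × (pA + pB)/2, with 547 = 576 × 0.95

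| a | pA | pB | Apparent HR | Two-sided type I error (nominal 5%) |
|---|---|---|---|---|
| 0.59 | 0.582 | 0.588 | 0.985 | 5.2% |
| 0.69 | 0.579 | 0.591 | 0.97 | 5.9% |
| 0.84 | 0.575 | 0.595 | 0.95 | 7.9% |
| 1.00 (allocation known) | 0.570 | 0.600 | 0.92 | 11.4% |

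For the assumed error rate these are upper bounds. The calculation treats every first event as open to being downgraded, although some are deaths, and it lets no later event replace a lost one.

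**The case against.** **Blinding has not been shown to fail.** A reader might infer that the committee is effectively unblinded. The document does not support that. Rescue iron can be given in both arms, study iron is withheld above the stated limits, the entry range for ferritin is wide (700 to 2000 μg/L), and the Background notes that ferritin also rises with inflammation. All of this blurs the pattern, and no unmasking rate is given. This stands, and it is why the point is limited to blinding not being secured.

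**The verifiers may be masked.** A reader might infer that unblinded investigators settle the endpoint. The general sentence does say that investigators are not blinded, but the same section says those assessing the primary outcome are. The verifiers' status is therefore unclear. Nor is verification said to override the committee's majority, so two rival final arbiters are not established. The open scope of verification remains.

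**Treatment detail is excluded.** The sentence that admits concomitant medication changes also bars treatment detail and restricts the data to changes linked to study outcomes. On that wording study iron is left out. This stands for medication entries. It does not reach the blood results, which are listed without restriction.

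**Ferritin may be relevant.** As an acute phase protein it cannot be called irrelevant to infection. But CRP is measured in the same monthly bloods, and a long ferritin and TSAT series is hard to justify for judging one admission.

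**Early stopping.** It is tempting to say that leaning calls would drive the stopping rule. The interim section uses the same composite ("Using the Haybittle-Peto rule, and the differences according to treatment allocation in risk of hospitalisation with all-cause infection or death") but does not say that the events will be adjudicated, so that link is only an inference.

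**Conclusion.** The concern holds in a limited form. The protocol sets a standard of no direct or indirect evidence of allocation but does not apply it to the initial extract, which includes serial ferritin, TSAT and haemoglobin. It also lets assessors read records that can show iron administration, and it leaves the chief investigators' masking and remit unstated. The passages under Who is blinded {17a} and Blinded endpoint assessment and adjudication need to be reconciled.

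The size is uncertain. Under an assumed 1-in-20 downgrade, inference at 59% to 84% accuracy moves the apparent hazard ratio to between about 0.985 and 0.95. The value of 0.92 applies only if allocation is fully known. The downgrade rate and the marker separations of 1 and 2 SD are assumptions; the 59% comes from the protocol's own haemoglobin figures for one value and says nothing about a series read with ferritin and TSAT. The sample size calculation is not in question. Because the remedy is cheap and the safeguard central to the design, the change should be made.

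**What to change.** Under Blinded endpoint assessment and adjudication:

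- Apply the existing direct-or-indirect-evidence test to the initial extract as well as to later requests.
- Replace the entry for all blood results with results relevant to judging infection around the admission, for example cultures, white cell count and CRP.
- Remove serial ferritin, TSAT, other iron indices, liver iron, and iron and ESA entries. Include haemoglobin only where the judgement needs it.

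Under Who is blinded {17a}:

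- Mask iron and ESA administration in the assessors' material as far as practicable.
- Limit the chief investigators' verification to completeness checks on masked forms.
- State that the three-member majority is final.

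The cost is modest. The committee's extract is already to be prepared, so filtering it is a change to the export and the wording. Masking the assessors' material takes more work, because they use electronic and written records for all randomised participants. No treatment rule changes.

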### Plans to promote participant retention and follow-up {18b}

The study team makes regular contact (either by phone or preferably in person on the units) with the participants’ treating teams at 3 months and every 6 months. The purpose of this contact is to check compliance with the protocol in terms of study drug prescribing and ordering of routine clinical blood tests. Data is collected and entered into the corresponding visit CRF. Standard operating procedures (SOPs) will contain step by step details on how to recruit patients, collect data and monitor progress.

Participants have the right to choose to withdraw from the study at any time and the investigator may discontinue a participant from the study or from treatment if deemed appropriate at any time. This will have no impact on their normal dialysis and other treatment or care. Reasons why a participant may be withdrawn from the study include, but are not limited to, participant request, primary treating clinician’s request, participant was enrolled and is ineligible (either arising during the study or was overlooked at time of screening and enrolment). Participants will not be withdrawn due to adverse events. The decision to withdraw a participant from the study must be discussed with the coordinating investigators.

If the participant withdraws consent from participating in the study and also withdraws consent for collection of future information, no further evaluations will be performed, and no additional data will be collected. The sponsors may retain and continue to use any data or samples collected before such withdrawal of consent. Participants that are lost to follow-up will continue to be followed by collecting as much data as possible, if possible, until the end of the trial to avoid missing data. Participants withdrawn from the treatment by the treating clinicians will continue to be followed up to the end of the trial to avoid missing data and will be used in the intention-to-treat analysis. This study has allowed for 5% of participant drop-out. Withdrawn participants will not be replaced.

If a participant is withdrawn, the reason is recorded in REDCap.

### Data management {19}

Source documents are those where data are first recorded, and from which participants’ CRF data are obtained. These include but are not limited to hospital records both electronic and paper (which will include medical history, previous and current medications, any relevant radiography test, blood test results, haemodynamic parameters, and medical correspondence) and paper or electronic clinic records (which include vital status, recent medical history and relevant blood culture results). A further potential data source will be through telephone conversations with the study participant or their primary doctor or general practitioner.

Storage and archiving of study documents (CRFs and consent forms) are the responsibility of the site principal investigator and these will remain at the site of recruitment.

Data for this study is recorded via a secure, Electronic Data Capture (EDC) web-based system (REDCap). It is transcribed by the study team from the paper CRFs into REDCap. Data is stored in a re-identifiable manner in the database, using the unique screening number for each patient. The database contains validation ranges for each variable to minimise the chance of data entry errors. An audit trail will maintain a record of initial entries and changes made; reasons for change; time and date of entry; and username of the person who made the change. Data queries are raised by the Clinical Trial Manager and study monitor, and missing data or suspected errors are raised as data queries and resolved prior to database lock and analysis. The database contains in-line capability so that these queries and answers are logged as part of the audit trail.

For each potential participant screened (including screen failures), the screening eCRF is completed by the study team. For each participant enrolled, eCRFs must be completed. This also applies to records for those patients who fail to complete the study. The study team should ensure the accuracy, completeness and timeliness of the data reported in the eCRFs and in all required reports. A comprehensive validation check programme verifies the data and automatically generates discrepancies for resolution by the study team. Manual discrepancies can also be raised if necessary.

In addition, for selected data fields, accurate and reliable data collection is assured by verification of the eCRFs against the study team’s records by the study monitor (source document verification), and the maintenance of medication compliance is captured in the CRFs from the participant’s medication chart (source document) by the study team.

